#### Ten-week VR Interventions

##### Culturally Adapted VR-CBT as the Active Condition

The culturally adapted therapy is a manualized CBT with an emotion regulation focus. The VR-CBT therapy will take place in a clinical setting and will consist of traditional therapeutic processing complemented by therapist-guided training in a VR environment. The main therapeutic strategies are stress inoculation and guided mastery with biofeedback components. Our group developed 2 VR environments (SB UQO [Université du Québec en Outaouais] cyberpsychology laboratory)—one for safe practice and the other for challenging emotion regulation skills. The first, called Snowy Place, is a snowy tundra that mimics the arctic life well known to Inuit. In developing Snowy Place, the Inuit advisory committee believed that this would be a comforting environment. The second is a small environment with many people and no children (small stressors), where the environment and elements (eg, social and situational) demand emotion regulation skills. The participant will train learned emotion regulation skills using these environments under the guidance of a psychotherapist. The VR-CBT can have interactive components where partial avatars (eg, hands of the participant) and preprogrammed avatars (eg, static or acting people in the room) are present. Multimedia Appendix 1 provides a detailed overview of the CBT therapist manual, including a session-by-session overview.

##### Calm Place as the Active Control

During the use of the VR application, the Calm Place user may see flowing water, mountains, and tree cover; a tropical atoll with sand, palm trees, and the ocean; or an arctic scene with large pines, snow cover, and large stones. In Calm Place, each virtual environment offers applications [25,28], such as visual breathing aids, time and weather cycles, and meditation voice overs, with the guidance of the VR program. Here, the guidance on relaxation is nonpersonalized and is based on the selections of the user within the VR environment. Thus, though participants’ weekly choices regarding prevalence and duration of use are self-managed and done from their home, this intervention involves guided programming for guidance. The self-management program—Calm Place—does not have any avatar, social-interactive, or personalized components. The research team will contact these minimal-attention control participants weekly to check whether they use the application and to verify their safety.

#### Translation

A professional translator translated each of the self-reported measures that did not have the existing French versions. For comparability, given the small sample size, the surveys will be administered in either English or French for data collection, and the language controlled for in statistical analysis. However, each psychometric measure was translated to Inuktitut to complement the understanding of English and French surveys.

#### Data Collection

##### Week 0: Screening, Consent, and Randomization

Before their participation, participants will be fully informed by research assistants about their role in the study and treatment options; if willing to participate in either of the treatments, adults or guardians will sign an informed consent form (study procedures in Figure 1). The number of participants rejecting one or another treatment and thus excluded from the actual trial will be registered for evaluation of acceptance. Initial visits will involve checking eligibility and preference for treatment. We then randomly assign participants to one of the 2 VR interventions—Calm Place or VR-CBT—for a maximum of 10 weeks.

The participant study procedures from recruitment until the end of participation include a baseline measurement, a 10-week intervention period, and follow-up.

**Figure 1 figure1:**
[figure not shown]
Flow of proof-of-concept study. VR: virtual reality.

##### Week 0: Baseline Measurement of Subjective and Objective Outcomes

At the first evaluation done in the days before the intervention, we evaluate the baseline subjective and objective measurements. Data will be collected and stored with REDCap (Research Electronic Data Capture) data collection software (Vanderbilt University), protecting the confidentiality of patients with research IDs. We will collect data on participants’ rest and stress psychophysiology during a 1-hour reactivity testing paradigm, where VR exposure will evoke relaxation (forest walk) or moderate stress (height exposure). Baseline measures include the Difficulties in Emotion Regulation Scale (DERS)-16 [29]; Clinical Outcome Routine Evaluation-Outcome Measure (CORE-OM) and Clinical Outcome Routine Evaluation- 10 item (CORE-10) [30,31]; Warwick-Edinburg Mental Well-being Scale (WEMWBS) [32,33]; Generalized Anxiety Disorder 7-item (GAD-7) [34]; Primary Care Screen for Posttraumatic Stress Disorder for Diagnostic and Statistical Manual 5 version (PC-PTSD-5) [35]; Patient Health Questionnaire 9-item (PHQ-9) [36]; visual analog scales for anxiety, emotional arousal, and emotional valence [37-40]; DAST-10 [41]; AUDIT-C [42]; and Severity of Dependence Scale for Cannabis (SDS-C) [43]. We will measure blood pressure using a calibrated, Health Canada–approved device. Figures 1 and 2 show the study flow diagram.

**Figure 2 figure2:**
[figure not shown]
SPIRIT (Standard Protocol Items: Recommendations for Interventional Trials) flow table. VR: virtual reality, VR-CBT: virtual reality–assisted cognitive behavioral therapy.

##### Weeks 1 to 10: Intervention Period and Weekly Questionnaires

During the intervention period, we will send participants biweekly questionnaires. In their final visit, participants will repeat the procedures from the first visits (visits 1 and 2). Participants will receive a small financial compensation (gift card) for each visit.

##### Week 10 to 11: Repeat Measure of Subjective and Objective Measurements

Once the intervention is complete, participants repeat the questionnaires and the reactivity testing paradigm from week zero to provide a second measurement.

##### Week 22: Postintervention Follow-up

Twelve weeks after their final visit, we will follow up with the participants on all baseline questionnaires.

### Materials

To support the delivery of the interventions and the corresponding collection of data during the trial, a sensor management system and web-based clinician portal were developed in collaboration with the National Research Council Canada (DJ and CP). The sensor management system facilitates the connection and initialization of the biofeedback sensor, eVu TPS (Thought Technology Ltd) as well as the streaming of data to the web portal. The web portal allows the management of participant sessions as well as live and postsession biofeedback data visualization. The raw biofeedback data (in CSV format) are also available through the portal to study coordinators and clinicians for postprocessing and analysis.

### Measures

#### Primary Outcome Measures

### DERS-16 Scores

The DERS-16 is a short, valid measure of emotion regulation [29,44]. Participants rate their ability to accept and be aware of their emotions, direct themselves toward their goals, control their impulses, access regulation strategies, and have emotional clarity [45]. The DERS’s psychometric properties are favorable, having moderate to very strong internal consistency (α=.69-.97) and strong retest reliability (*r*=0.88; ρI=0.85) [29, 46-49]. Correlating with anxiety, depression, stress, borderline traits, and more, the DERS-16 has good construct validity [29,47,50]. Although consistent across demographics and culturally adapted for some groups, the scale is not yet adapted for any Indigenous groups [48,51]. The full DERS is translated into French and validated [52]. Although there are no formal cutoff scores for the DERS, the English scale achieves moderate diagnostic accuracy (area under the curve [AUC]) among emotional disorders and nonsuicidal self-injury populations [53-55], and it is sensitive to changes following treatment [56-60].

### Visual Analog Scales: Anxiety, Emotional Arousal, Emotional Valence

Participants will respond to the Visual Analog Scale (VAS)-Anxiety (VAS-A), Visual Analog Scale-Emotional Arousal (VAS-EA), and Visual Analog Scale-Emotional Valence (VAS-EV) during reactivity testing. These items have favorable properties, including construct validity and sensitivity [37-40].

### Objective Measures

The participants will undergo a psychophysiological reactivity testing paradigm. This will be repeated after the end of the VR intervention for those who completed a minimum of 7 and a maximum of 10 sessions of therapy as soon as possible after the final session. We will collect and measure several metrics, including heart rate, blood volume pulse, skin conductance, blood pressure, and accelerometer data. Participants first respond to baseline subjective arousal, emotional arousal, and VAS-EV. We then begin collecting psychophysiological data with a portable finger sensor, covered with a piece of cloth for light sensitivity, by attaching it to the participant’s nondominant index finger. They fill out a survey, including several symptom scales as described during this approximately 15-minute period, and have their blood pressure taken with an ambulatory blood pressure machine. We also record a no-task seated baseline recording of sensor data for 3 minutes. Then, participants will familiarize themselves with VR in a forest walk environment with no tasks other than to walk and explore (5.5 minutes), with minimal interaction with the research team. In the next segment, participants walk a VR plank exposing them to the heights below for 5.5 minutes (instructed to walk back and forth, with no interaction). If the exercise is too challenging (eg, participant distress at a tolerable level), participants remain in the environment without walking for 2 minutes or withdraw completely (eg, intolerable distress) from the exercise. Finally, participants re-enter the same VR environment, this time with a floor rather than a plank beneath them and walk (3 minutes). The last segment is a 10-minute seated rest period. After each segment, participants report using the same visual analog scales.

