**Methods:**

Trial participants will be randomly assigned to an active condition or active control condition in a 1:1 ratio. Inuit aged 14 to 60 years will receive a culturally adapted and therapist-guided VR-CBT with biofeedback or a VR relaxation program with nonpersonalized guided components over a 10-week period. We will collect pre- and posttreatment measures of emotion regulation and biweekly assessments over the treatment and at 3-month follow-up. The primary outcome will be measured by the Difficulties in Emotion Regulation Scale (DERS-16) and a novel psychophysiological reactivity paradigm. Secondary measures include psychological symptoms and well-being via rating scales (eg, anxiety or depressive symptoms).

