##### Feasibility: Attrition and Adherence

We will collect data about the feasibility of the treatment in the form of weekly use data (Calm Place group) and study attrition and adherence to treatment (VR-CBT group). These metrics will be assessed by the number of treatment sessions attended, completion of treatment, percentage of sessions attended, number of patients who dropped out, and when possible, reasons for dropping out, comments and notes on feasibility in diary responses, the time spent using the program, and consistency in using the program over 10 weeks. Treatment completers for VR-CBT will be defined as individuals who attend 7 out of 10 sessions, and for Calm Place, 7 reported sessions over 10 weeks. Dropouts for VR-CBT are defined as individuals missing 2 consecutive sessions of therapy without rescheduling (no-show). Noncompleters are individuals who complete <7 sessions (but attend at least 1). In the case participants are judged by the research team as *at risk* (eg, psychologically), they may also be withdrawn from the study.

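### One section limits the post-treatment reactivity test, one of two primary measures, to participants with 7 to 10 sessions, so its between-arm contrast is completers-only as written

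*Protocol article*

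**What the plan says.** The abstract's Methods paragraph puts the reactivity test on the same footing as the rating scale: "The primary outcome will be measured by the Difficulties in Emotion Regulation Scale (DERS-16) and a novel psychophysiological reactivity paradigm". The body of the protocol article also places it under Primary Outcome Measures.

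Three sections say who repeats it after treatment:

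- Objective Measures: the test is "repeated after the end of the VR intervention for those who completed a minimum of 7 and a maximum of 10 sessions" of therapy, with the test to follow promptly after the last one.
- Weeks 1 to 10: "In their final visit, participants will repeat the procedures from the first visits (visits 1 and 2").
- Week 10 to 11: "participants repeat the questionnaires and the reactivity testing paradigm from week zero to provide a second measurement".

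Only the first carries a session threshold. The same number defines completion under Feasibility: Attrition and Adherence: "Treatment completers for VR-CBT will be defined as individuals who attend 7 out of 10 sessions, and for Calm Place, 7 reported sessions". Below it, "Noncompleters are individuals who complete <7 sessions (but attend at least 1"). No section provides for retesting noncompleters.

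Objective Psychophysiology Data Analyses then plans regression models for change from baseline to after the intervention, and an effect size between groups A and B.

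**The concern.** The number of sessions completed is known only after randomisation and may depend on the treatment. If the second test is given only to those who reach seven sessions, the groups compared on it are no longer the groups that were randomised. The visual analog scales taken during the test are lost with it.

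Three features of the protocol make unequal selection plausible:

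- VR-CBT sessions are counted by attendance at the clinic, whereas Calm Place sessions are reported by participants who choose at home how often to use the program.
- Strengths and Limitations suggests that therapist guidance and cultural adaptation could improve attendance in the VR-CBT arm.
- It is unclear whether the threshold applies to Calm Place at all, because Objective Measures speaks of sessions of therapy and does not refer to the completer definition.

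The trial is meant to choose outcome measures and supply power calculations for a larger trial, and to judge whether the psychophysiological measures are feasible and valid. A completers-only effect size would be carried into that planning. The trial would also not learn whether people who stop early can be retested.

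**Working it through.** **The sections side by side.** Take a participant with five sessions. Under Objective Measures there is no second reactivity test. Under Weeks 1 to 10 and Week 10 to 11 there is one. Staff cannot follow both. If Objective Measures is followed, the contrast has two possible forms:

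- Threshold binds both arms: VR-CBT completers against Calm Place completers.
- Threshold binds VR-CBT only: VR-CBT completers against all controls.

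**Size of the bias.** The protocol gives neither a noncompletion rate nor a difference between completers and noncompleters, so both are assumed here. Let q be the noncompletion share in an arm and δ the number of SDs by which noncompleters do worse.

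- Mean of all randomised = (1 − q) × completer mean + q × (completer mean − δ) = completer mean − qδ.
- So the completer mean is too favourable by qδ within that arm.
- Bias in the between-arm contrast = difference in qδ between arms.

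With q = 0.2 in one arm and 0.4 in the other, and the same δ in both:

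- δ = 0.5: (0.4 − 0.2) × 0.5 = 0.10 SD
- δ = 0.8: (0.4 − 0.2) × 0.8 = 0.16 SD
- Equal qδ in both arms: 0

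A second model supports this. Let completion and outcome have correlation ρ, with no true treatment effect. The completer mean shifts by ρφ(z)/p, where p is the completion rate, z the normal quantile at 1 − p and φ the normal density. The factor φ(z)/p is 0.350 at p = 0.8 and 0.644 at p = 0.6. The between-arm bias is then ρ × 0.294, which is 0.09 SD at ρ = 0.3 and 0.15 SD at ρ = 0.5. At 80% completion in both arms it is zero.

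**Precision.** The Sample Size section states power 0.97 for 20 per arm with df=38. That figure is not reproduced at α = 0.05. A two-sided noncentral t calculation gives 0.67 at g=0.78 and 0.79 at g=0.90; the printed alpha of .5 gives 0.96 and 0.985. This is a separate matter and the present point does not depend on it. The baseline used here is the recomputed 0.67.

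Noncentrality = d × √(n₁n₂/(n₁+n₂)), df = n₁+n₂−2, d = 0.78 (the protocol's figure against minimal-attention controls), two-sided α = 0.05:

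| Tested | Noncentrality | Critical t | Power |
|---|---|---|---|
| 20 v 20 (all randomised) | 2.467 | 2.024 | 0.67 |
| 14 v 14 (30% noncompletion, both arms filtered) | 2.064 | 2.056 | 0.51 |
| 14 v 20 (30%, VR-CBT arm only filtered) | 2.238 | 2.037 | 0.58 |

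**The case against.** The strongest reply is that this is a proof-of-concept trial whose aims are feasibility, benefits and challenges, and that the psychophysiological measures are themselves under study. Looking at an experimental marker only after adequate exposure is a defensible choice. That stands as a reason to keep a completer analysis. It does not justify an unlabelled between-arm effect size computed on completers.

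Several stronger readings are tempting, but the protocol does not support them.

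- A reader might infer that the whole randomised comparison becomes completers-only. It does not. DERS-16 is the measure named for the between-arm mixed model, and no section attaches a session threshold to it or to the other questionnaires. Questionnaires are also collected biweekly and at week 22. Some symptom scales are filled in during the test visit, but the Week 10 to 11 section schedules the questionnaires without any threshold.
- A reader might take it as settled that each arm is filtered by its own count. The wording leaves open whether Calm Place is filtered at all.
- A reader might see a timing conflict between testing soon after the final session and testing at week 10 to 11. In a 10-week programme these normally coincide and diverge only when someone finishes early.
- A reader might say that no analysis could help. Baseline reactivity and serial questionnaire scores would allow modelling, but only under assumptions that cannot be tested, because the values were never collected.
- Participants judged at risk "they may also be withdrawn from the study". A reader might infer that the most distressed are systematically lost. The text does not say that, and withdrawal is a clinical decision for the investigator.

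**Conclusion.** The point holds for the reactivity test and the visual analog scales taken during it. As Objective Measures is written, their between-arm contrast is conditioned on a post-randomisation variable, and that section contradicts the two data-collection sections.

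Neither the size nor the direction of the bias can be derived from the protocol. The 0.10 to 0.16 SD rests on assumed noncompletion of 20% in one arm and 40% in the other, with noncompleters 0.5 to 0.8 SD worse in both. The shift within a single arm (0.2 × 0.5 = 0.10 to 0.4 × 0.8 = 0.32 SD) should not be read as bias in the treatment contrast when both arms are filtered, because equal shifts cancel. The fall in power is a loss of precision, not bias, and assumes that every noncompleter would have returned for testing. The matter should be settled before data collection, because a missed post-treatment test cannot be obtained later.

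**What to change.** Reconcile Objective Measures with the Weeks 1 to 10 and Week 10 to 11 sections by removing the session threshold. Suggested wording: the week 10 to 11 reactivity test is offered to every randomised participant in both arms, whatever the number of sessions completed, subject to consent and the investigator's safety judgement.

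In Objective Psychophysiology Data Analyses, state that the reactivity contrast is analysed by allocated arm. Keep the 7-session subset as a supportive analysis labelled completers-only. The questionnaire schedule needs no change, and the rule on withdrawing participants at risk stays with the investigator.

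Cost: a wording amendment and, at the assumed 20% to 40% noncompletion, 40 × 0.2 = 8 to 40 × 0.4 = 16 extra one-hour assessments across both arms. At the protocol's compensation of about CAD $15 per hour, that is roughly CAD $120 to $240 in gift cards, plus staff time. Fewer will be needed if some noncompleters decline.

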#### Secondary Outcome Measures

##### PC-PTSD-5 Scores

On a scale of 5 items, the PC-PTSD-5 first verifies trauma exposure and then evaluates the presence of the 4 symptom clusters of PTSD [35]. The 5 items include symptoms such as arousal, re-experiencing, avoidance, and negative cognitions and mood. The scale has strong test-retest reliability (*r*=0.83) and is associated with important clinical variables such as suicide [35,61]. With a cutoff score of 3, the PC-PTSD-5 has strong diagnostic accuracy (AUC=0.941) [35]. The scale was translated by the Clinical Psychology and Psychotherapy Unit of the Bielefeld University into French [62].

##### WEMWBS Scores

The WEMWBS with both its 14-and short 7-item versions, measures holistic aspects of well-being. The dimensions include eudemonic aspects, hedonic aspects, psychological functioning, and subjective well-being [32,33]. Positive mental health provides an independent factor for functionality in the presence or absence of a mental illness. This scale has favorable psychometric properties. Using the WEMWBS, we can calculate mental health costs and quality-adjusted life-years [63,64]. In a study of Indigenous Australians, the Short-Form WEMWBS achieved an internal consistency of α=.69 to .88 [65]. The WEMWBS has also been evaluated in various minority and cultural groups [66].

##### GAD-7 Scores

The GAD-7 [34] is a validated self-report scale that measures anxiety presence and severity [67]. Among outpatients with anxiety and mood disorders, the GAD-7 is a reliable (*P*=.85) and sensitive (79.5%) measure with a cutoff score of 10 [68]. The GAD-7 scores have been categorized into mild, moderate, and severe anxiety, with cutoffs of 5, 10, and 15 [34,68]. Among Indigenous students in Canada, the GAD-7 achieved an internal consistency of α=.86 and correlated strongly with related constructs [69]. The scale was translated and validated in French [70].

##### PHQ-9 Scores

The PHQ-9 is a depression severity measure based on the Diagnostic and Statistical Manual Version IV [36]. In a meta-analysis of the scale’s psychometric properties, the PHQ-9 achieved optimal sensitivity and specificity with a cutoff score of 10 [71]. Among Indigenous North Americans, the scale’s psychometric properties were favorable, with an internal consistency of α=.94 [72].

##### CORE-OM, 10-Item Version

The CORE is widely used as an outcome measure in psychotherapy and has several versions, including the CORE-OM and the 10-item version CORE-10 [30,31]. The CORE-OM and CORE-10 are screening measures for psychological distress, including items for well-being, psychological symptoms, functioning, and risk. The CORE-OM has excellent internal consistency in clinical samples (α=.94) and for each of its subscales (α=.75-.94); it also has good test-retest reliability (*P*=.83) [73]. The CORE-10 with a cutoff score of 11 differentiated between clinical and nonclinical general samples with a sensitivity of .85. Its internal consistency was α=.90, and it had a reliable change index of 6 points [30]. The widely accepted French translation had validity results forthcoming from the University of Toulouse [74].

